For Study 3, a minimum of 15 individual Think-Aloud Protocol sessions will be held with adoptive parents. Qualitative data will be analyzed by using thematic analysis [54] via the NVivo14© software program. All video and audio recordings of the sessions will be transcribed. On the basis of these transcripts and notes taken during the sessions, usability issues will be identified and rated according to their severity: minor, medium, or critical. Bugs will also be flagged and later reported to web developers. All usability issues rated as medium or critical will be coded on the basis of their content and subsequently mapped according to two predefined categories: navigation or functionality. After this categorization, the categories will be cross-referenced with the general “usability heuristics for users interface design” [55]. These heuristics are often used by experts in the field of user-experience design to inform design decisions, since they offer a set of valuable guidelines developed over decades for designing systems, identifying usability problems and creating better user experiences. The quantitative data will be analyzed via SPSS. Descriptive statistics will be used to explore the perceptions of adoptive parents regarding the prototype version of *AdoptMindful2Care@Web*.

In Study 4, 60 participants (30 per condition; 95% CI, power of 0.99, medium effects, repeated measures ANOVA, and within–between interaction; G*Power [53]) will be needed in the final evaluation. Owing to the expected dropout rate of 60% in e-health interventions [56], we will recruit a total of 96 participants. Statistical analyses will be conducted via IBM SPSS. Descriptive statistics will be used to evaluate the feasibility and acceptability of *Adoptmindful2Care@Web*. Repeated measures ANOVAs/linear mixed models (timeXgroup interaction) will be used to analyze the modifications in participants’ outcomes at the four different assessment times.

In Studies 1, 2, and 4, sociodemographic, clinical, and/or child-related variables will be controlled for in all statistical analyses, in order to account for possible differences between adoptive parents.

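### Study 4's dropout allowance multiplies by 1.6 instead of dividing by 0.4: recruiting 96 at 60% dropout leaves about 38 participants, not the 60 required

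*Protocol article*

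**What the plan says.** The Study 4 sample size is given in two consecutive sentences of the protocol article, section 2.5 (Sample Size and Statistical Analyses).

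- The first sets the target: "60 participants (30 per condition; 95% CI, power of 0.99, medium effects, repeated measures ANOVA, and within–between interaction". It says that this number "will be needed in the final evaluation", so 60 is the count at the end of the study and not the count randomised.
- The second gives the recruitment figure and its reason: "Owing to the expected dropout rate of 60% in e-health interventions [56], we will recruit a total of 96 participants".

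The same paragraph names repeated measures ANOVAs or linear mixed models, with a time-by-group interaction, for outcomes "at the four different assessment times". The article gives no separate dropout rate per arm, no rule for replacing participants who leave, and no other dropout figure for Study 4.

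**The concern.** The 96 is presented as what must be recruited so that 60 are left after 60% dropout. If six in ten leave, only four in ten of those recruited remain, and four tenths of 96 is well below 60. It looks as though the dropout percentage was applied to the target and added on, when the target should have been divided by the proportion retained.

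Two things are at stake.

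- **Power.** The quoted power of 0.99 is attached to 60 participants at the end. If dropout runs as the plan itself predicts, the trial misses that number.
- **Interpretation of the pilot.** Dropout rate is one of the listed feasibility measures for Study 4 (Table 1), and the results are meant to shape a larger randomised trial (sections 3 and 5). A trial that behaves exactly as expected would appear to have failed its own sample-size target. The same formula could also be carried into the larger trial, where the cost would be greater.

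**Working it through.** **Inputs from the article (section 2.5)**

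- Needed at final evaluation: n = 60 (30 per condition)
- Expected dropout: d = 0.60
- Planned recruitment: N = 96 (48 per arm, taking equal allocation)

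**Step 1. Reproduce the stated 96**

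- Adding the percentage to the target: n × (1 + d) = 60 × 1.60 = **96**, an exact match.
- Dividing by the proportion retained: n / (1 − d) = 60 / 0.40 = **150** (75 per arm), which does not match.

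**Step 2. What 96 delivers**

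- Expected remaining: 96 × 0.40 = **38.4**, about 19 per arm.
- Shortfall: 60 − 38.4 = 21.6, and 21.6 / 60 = **36%**.
- Dropout at which 96 gives 60: 1 − 60/96 = **37.5%**.
- If each participant remains independently with probability 0.40, the chance that at least 60 of 96 remain is about 7 in a million (binomial). Ordinary variation would not close the gap.

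**Step 3. Could the 60% apply to the web arm only?** The article does not say so.

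- Web arm: 48 × 0.40 = 19.2, about **19** against the required 30.
- Control arm with no loss: 48. Total: about **67**.

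The total then exceeds 60, but the per-condition requirement still fails in the intervention arm.

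**Step 4. Effect on the stated power**

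The article gives a power of 0.99 and a medium effect, but no numerical effect size, correlation between repeated measures or sphericity correction. The figures below therefore rest on assumptions: f = 0.25, α = 0.05 (read from the 95% level quoted), sphericity, and a correlation ρ of 0.5 or 0.3. For a within–between interaction with k = 2 groups and m assessments, power comes from the noncentral F distribution with

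λ = f² × N × m / (1 − ρ), df1 = (k − 1)(m − 1), df2 = (N − k)(m − 1).

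For example, with N = 38, m = 4 and ρ = 0.5: λ = 0.0625 × 38 × 4 / 0.5 = 19.0, df1 = 3, df2 = 108, power 0.962.

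| Participants at the end | m | ρ = 0.5 | ρ = 0.3 |
|---|---|---|---|
| 60 | 3 | 0.991 | 0.953 |
| 60 | 4 | 0.998 | 0.980 |
| 38 | 3 | 0.922 | 0.805 |
| 38 | 4 | 0.962 | 0.873 |

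With ρ = 0.5 and three assessments, 60 is the smallest even total that reaches 0.99, so these assumptions are a plausible reconstruction of the plan's calculation. Both values of m are shown because section 2.4 speaks of three assessment times but lists four, T0 to T3.

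**The case against.** Four points can be made for the plan.

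1. **The 60% may describe the intervention only.** The article speaks of dropout in e-health interventions, and control parents receive nothing to drop out of until the study ends. On that reading about 67 remain. A 19/48 split carries the information of about 4 × 19 × 48 / 67 = 54 balanced participants, with power of about 0.985 (m = 3) or 0.996 (m = 4) at f = 0.25 and ρ = 0.5. This stands as a limit on the consequence: 38 is the figure if both arms lose 60%. It does not reconcile the text, which states one rate, inflates the whole sample by it, and asks for 30 in each condition.

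2. **Linear mixed models can use partial data.** Participants who leave after baseline can still contribute, so the number analysed may exceed the number of completers. This is true, but the plan defines its requirement at the final evaluation, and repeated measures ANOVA, on which the sample size is based, uses complete cases in its standard form.

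3. **Power remains fairly high.** The target of 0.99 is generous, so 38 completers still give 0.92 to 0.96 at ρ = 0.5, and 0.81 to 0.87 at ρ = 0.3. This stands, and it is why no larger sample need be demanded.

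4. **Study 4 is a pilot.** Its aims are feasibility, acceptability and preliminary efficacy, with a larger trial to follow. That makes 96 a defensible number to recruit. It does not make 96 the correct allowance for 60% dropout.

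**Conclusion.** The concern holds. 60 needed, 60% dropout and 96 recruited are mutually inconsistent, and the exact match to 60 × 1.6 points to the wrong inflation formula. At the stated dropout in both arms, about 38 participants are expected at the final evaluation, 36% below target. If the loss is confined to the web arm, that arm still ends with about 19 of the 30 required.

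This arithmetic uses only figures in the article. The power consequence depends on the assumed f, ρ and sphericity. Under f = 0.25 and ρ = 0.5 the loss is moderate, from 0.99 or above at 60 to between 0.92 and 0.96 at 38. The statement should be corrected because it is wrong in the headline sample size, although the trial remains workable at 96.

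**What to change.** Correct the sample-size paragraph in section 2.5 in one of these ways.

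- **Keep 96 and report what it gives.** Suggested wording: *With 96 participants recruited and 60% dropout, we expect about 38 (19 per arm) at the final evaluation; 60 would be reached only if dropout were at most 37.5%, and 60% dropout would require recruiting 150.* Restate power and precision for 38, giving the effect size f, the correlation, the number of assessments and any sphericity correction used.
- **Keep 96 and the target of 60.** Replace the 60% with a justified dropout rate of at most 37.5%.
- **Keep 60 and 60%.** Recruit 150.

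If the 60% is meant for the web arm only, say so, state the rate expected in the control arm, and give the expected number per arm.

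The first two options need only text changes and no extra participants; the cost is that the stated figures become less favourable or need a new justification. The third adds 150 − 96 = 54 participants and is not necessary for a pilot.

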For Study 3, the e-mail will contain the link to the form with information about the objectives of the study. Through this link, respondents can express their interest in participating, provide their contact details, and provide permission to be contacted by the research team to schedule the session. The sessions will take place in person in a space belonging to the university that hosts the project. The participants will have access to a computer on which the intervention platform will be made available. They will be instructed to guide their own use of the platform—with the aim of bringing this experience closer to its real use—while simultaneously receiving an opportunity to express their thoughts about it. If needed, the participants will be prompted to keep talking during the session. Video and audio recordings will be made, and written notes will be taken throughout the sessions for later analysis. To augment the information obtained during this task with a quantitative aspect, participants will also be asked to complete a self-report questionnaire at the end of the session.

In Study 4, an e-mail will contain a link to a website where interested respondents can find detailed information about the project and the intervention and through which they can complete a request to be contacted by the research team. This contact phone call will be used to explain the study and the intervention in more detail, answer questions, and verify eligibility. After eligibility is confirmed, the participants will be randomized into two groups: an experimental group, with immediate access to *AdoptMindful2Care@Web*, and a control group, with access to the intervention only at the end of the study. In both groups, participants will have to complete online self-report questionnaires, the link to which will be sent via e-mail, at three different times: T0 (preintervention), T1 (postintervention; for participants in the experimental group, the link will be sent 2 days after completing the last module of the intervention, and for the waiting group, 8 weeks after completing the T0 step), T2 (1-month follow-up), and T3 (2-month follow-up).

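### Study 4 leaves open repeated measures ANOVA or a linear mixed model; the ANOVA would reduce the efficacy analysis to completers under the dropout the plan expects

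*Protocol article*

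**What the plan says.** Section 2.5 of the protocol article gives the Study 4 efficacy analysis in one sentence: "Repeated measures ANOVAs/linear mixed models (timeXgroup interaction) will be used to analyze the modifications" in participants' "outcomes at the four different assessment times". The two methods are joined by a slash, and nothing says when each applies.

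The sample size rests on the first method: "60 participants (30 per condition; 95% CI, power of 0.99, medium effects, repeated measures ANOVA" with a within-between interaction. These 60 "will be needed in the final evaluation". The section then adds: "Owing to the expected dropout rate of 60% in e-health interventions", "we will recruit a total of 96 participants". The software is SPSS. The article describes no imputation or other handling of missed assessments.

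Section 2.4 announces questionnaires "at three different times: T0 (preintervention), T1 (postintervention" and so on, but then lists T0, T1, T2 and T3. Table 1 also shows four assessments, so four is used here. Section 2.4 also triggers the T1 link differently by arm: in the experimental arm by finishing the last module (plus 2 days), in the waiting arm by the calendar (8 weeks after T0).

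**The concern.** The two methods are not interchangeable when data are missing. Classical repeated measures ANOVA in SPSS needs one complete row per person, so a parent who misses a single assessment is removed together with every assessment that he or she did complete. A linear mixed model uses whatever each parent supplied.

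Three things are at stake.

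- **Bias.** A completers comparison is unbiased only if being a completer is unrelated to outcome and arm. The arm-specific T1 trigger makes that doubtful: read literally, an experimental-arm parent who never finishes the programme has no T1 trigger, while a waiting-list parent does. The mixed model needs the weaker assumption that missingness depends only on observed data.
- **Precision.** Collected assessments are discarded.
- **Choice after the fact.** With two primary outcomes, six secondary constructs and no rule, the method could be chosen once results are known.

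**Working it through.** **1. The plan's own figure.** Inputs from section 2.5: N = 60, two arms, power 0.99; the 95% CI is read as alpha 0.05. Assumed, because not stated: medium effect f = 0.25, correlation 0.5, sphericity. With m assessments, the noncentrality is f² × N × m / (1 − 0.5).
- m = 4: 0.0625 × 60 × 4 / 0.5 = 30, on 3 and 174 df; power 0.998.
- m = 3: 0.0625 × 60 × 3 / 0.5 = 22.5, on 2 and 116 df; power 0.991.

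The stated 0.99 reproduces, and it is a power for complete cases.

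**2. Who the ANOVA would exclude** (96 recruited, taken as 48 per arm).
- 60% loss in both arms: 96 × 0.40 = 38.4, so about 38 remain and 58 are dropped.
- The plan's own 96-to-60 step: 1 − 60/96 = 37.5% loss, so 36 are dropped. The 96 equals 60 × 1.6; a 60% loss would need 60 / 0.40 = 150. That is a separate sample-size problem.
- 60% loss in the experimental arm only: 48 × 0.40 + 48 = 67.2, so about 29 are dropped, leaving about 19 against 48.

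Intermittent missed assessments would add to each figure.

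**3. What this costs in power and precision.** Assumed: 48 per arm, 60% loss in both arms by T3 with no return, correlation 0.5 between all visits, a 0.5 SD difference at T1, T2 and T3, known covariance, and a 3-df time-by-group chi-square test at 0.05. Let n1, n2, n3 be the number per arm seen at T1, T2, T3. The noncentralities are:
- Complete cases, n per arm: 0.1875 × n. SE of the T1 effect: √(2/n).
- Mixed model with equal baseline means imposed: L = n1/6 + n2/12 + n3/20. SE at T1: √(2 × 0.75/n1).
- Ordinary time-by-group mixed model: L / (1 + L/24). SE at T1: √(2 × (0.25/48 + 0.75/n1)).

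Complete cases with n = 19: 0.1875 × 19 = 3.56, power 0.32 (0.31 with the F test), SE √(2/19) = 0.32 SD.

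| Cumulative dropout before T1/T2/T3 | L | Ordinary mixed model: noncentrality, power, T1 SE | Baseline-constrained: power, T1 SE |
|---|---|---|---|
| 60/60/60% | 3.2 + 1.6 + 0.96 = 5.76 | 5.76/1.24 = 4.65; 0.41; 0.30 | 0.50; 0.28 |
| 30/45/60% | 5.6 + 2.2 + 0.96 = 8.76 | 8.76/1.365 = 6.42; 0.55; 0.235 | 0.70; 0.21 |
| 20/40/60% | 6.4 + 2.4 + 0.96 = 9.76 | 9.76/1.407 = 6.94; 0.59; 0.22 | 0.75; 0.20 |

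**4. Separating two sources of gain.** With no missing data, L = 8 + 4 + 2.4 = 14.4. The constrained model then has power about 0.90 and the ordinary model 14.4/1.6 = 9.0, power 0.71. Complete-case ANOVA has the same noncentrality, 0.1875 × 48 = 9.0. The step from the ordinary to the constrained model is therefore baseline adjustment. Only the step from complete cases to the ordinary model is due to missing-data handling.

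**5. At the implied 37.5% loss,** all before T1 (n = 30 per arm). Complete cases: 0.1875 × 30 = 5.63, power 0.49, SE √(2/30) = 0.26. Ordinary mixed model: L = 5 + 2.5 + 1.5 = 9, 9/1.375 = 6.55, power 0.56, SE 0.25.

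**The case against.** The strongest reply is that the plan does not commit to the weaker method. The better one stands in the same phrase, and choosing between them is often left to an analysis plan, which is not shown. This stands in part. A reader might infer that the plan will throw away most randomised parents. The text does not support that: it permits the ANOVA without requiring it. The remaining point is still more than missing detail, because the protocol states the methods, one of them fits badly with its own dropout assumption, and the sample size rests on that one.

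Second, the 60% is cited as dropout in e-health interventions and may mean leaving the programme, which the waiting-list arm cannot do during the study. This also stands as a limit: the majority claim holds overall only if 60% of assessments are lost in both arms. The plan does, however, use the figure to inflate for the final evaluation.

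Third, the gain depends on timing. If parents leave before T1, they contribute only T0 and a mixed model can do little for them. The table shows this: 0.41 against 0.32 in that pattern.

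Fourth, on the plan's own basis (f = 0.25), 38 completers still give power 0.96 at correlation 0.5, 0.87 at 0.3 and 0.72 at 0. This is no contradiction: a sustained 0.5 SD difference corresponds to f of about 0.11, since 0.11 ≈ √[(0.1875² + 3 × 0.0625²)/4]. It does mean that the absolute powers depend on the assumed effect.

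Finally, this is a pilot, with a larger trial to follow.

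**Conclusion.** The point holds as an unresolved choice between two methods that are not equivalent here. If the ANOVA is chosen, between about 29 and 58 of 96 randomised parents leave the analysis, depending on how the dropout figure is read, and the result is a completers comparison.

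Under 60% loss in both arms and the stated assumptions, the ordinary mixed model has interaction power of 0.41 to 0.59 against about 0.32, and a T1 standard error of 0.30 to 0.22 SD against 0.32. It gains in every dropout pattern checked, but in the least favourable one the gain in precision is small. The known covariance slightly favours the mixed model.

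A reader might credit missing-data handling with the whole difference between complete cases and a baseline-constrained model (0.32 against 0.50 to 0.75). That would be wrong, since part of it is baseline adjustment and appears with complete data too.

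The more lasting argument is the weaker missing-data assumption, given dropout that may well differ by arm. The change should be made. Its weight is moderate, because the trial is a pilot and the better method is already named.

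**What to change.** In section 2.5, delete the repeated measures ANOVA alternative. State that each Study 4 outcome is analysed by a linear mixed model for repeated measures with time, group and time-by-group effects, optionally with a common baseline mean. It should include all randomised participants in their assigned arm and use every available assessment. Report a complete-case analysis only as a sensitivity analysis.

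The cost is one sentence; the method is already in the plan and runs in SPSS. The limits should be acknowledged: the model recovers little for parents with T0 only, and it does not remove bias if dropout depends on unobserved outcomes.

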oStudy 1, performed with adoption professionals, will use a survey developed by the research team for this purpose and is intended to explore the recommendations of such professionals regarding the content, format, and dissemination features required for AdoptMindful2Care@Web to meet (1) the needs expressed by adoptive parents when asking for professional support, (2) the professionals’ own needs when providing support for adoptive parents, and (3) the adoption system’s ethical and institutional requirements for the integration of AdoptMindful2Care@Web in the organizational structure and working routine of adoption services.oStudy 2, performed with adoptive parents as prospective users of AdoptMindful2Care@Web, will use a survey developed by the research team for this purpose to (1) characterize the literacy of adoptive parents regarding e-mhealth tools, (2) identify the mental health and parenting needs that such parents expect to be addressed by AdoptMindful2Care@Web, and (3) analyze the preferences and acceptance (perceived utility and availability for use) of such parents regarding AdoptMindful2Care@Web’s content, format, and dissemination features.Phase II, which will be dedicated to the design task. In this phase, the prototype of *AdoptMindful2Care@Web* will be developed on the basis of the information gained in Phase 1. The intervention’s content will be developed by the research team and systematically and interactively reviewed by researchers/clinicians in the adoption field. Technological features will be developed by a specialized IT company according to the guidance of the research team. This process will be monitored by LAICOS–Behavioral Change, a company specialized in behavioral science. In this phase, we will also perform Study 3, which is intended to test the usability of the prototype version of *AdoptMindful2Care@Web* with adoptive parents, using the Think-Aloud Protocol and a survey developed by the research team for this purpose.Phase III, which will be dedicated to operationalization and preliminary summative evaluation. The pilot version of *AdoptMindful2Care@Web* will be developed on the basis of the results of the previous phase. Then, we will perform Study 4, which is intended to assess the feasibility, acceptability, and preliminary efficacy of the intervention (i.e., improvements in parent and child outcomes at postintervention and/or follow-up) through a two-arm pilot randomized controlled trial. The results of this study will inform the necessary changes to be incorporated into *AdoptMindful2Care@Web* to establish its final version.

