			**Children 6–17 years old** **Pediatric Symptom Checklist** (PSC17 [48]): described above.
			**Children 2–4 and 4–17 years old** **Strengths and Difficulties Questionnaire** (SDQ [49]): described above.

Note: T0 = baseline assessment; T1 = postintervention assessment; T2 = 1-month-follow-up assessment; T3 = 2-month-follow-up assessment. * Primary outcomes. ** Secondary outcomes.

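### Study 4 tests efficacy by a time-by-group interaction with T0 as an outcome and no primary time point; adjusting for T0 raises power without added participants

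*Protocol article*

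**What the plan says.** All places are in the protocol article.

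- **Test (section 2.5).** Study 4 outcomes are to be analysed with repeated measures ANOVAs or linear mixed models: "timeXgroup interaction) will be used to analyze the modifications in" participants' outcomes over four assessment times, T0 to T3. The covariates named for all analyses are sociodemographic, clinical and/or child-related. The baseline value of the outcome is not among them.
- **Sample size (section 2.5).** "In Study 4, 60 participants (30 per condition" are needed, justified by "power of 0.99, medium effects" and the within-between interaction in G*Power.
- **What counts as preliminary efficacy (section 2.1, repeated in section 3).** It is described as "improvements in parent and child outcomes at postintervention and/or follow-up". No time point has priority.
- **Outcomes (Table 1 and its note).** Parenting stress (PSI-SF) and positive mental health (MHC-SF) carry the same primary mark. Child outcomes are secondary.

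**The concern.** There are two problems.

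1. **Baseline.** In a randomised trial the arms differ at T0 only by chance. A test that keeps T0 as a fourth response level spends information on estimating an arm difference at T0 that is zero by design. Using T0 as a covariate, or constraining its mean to be equal across arms, recovers that information.
2. **Target.** With time categorical and two arms, the interaction has (2-1)(4-1) = 3 degrees of freedom. A significant result says neither when the arms differ nor in which direction. To state improvement after the intervention and/or at follow-up, the team must make further per-time comparisons, and the description does not say which of them counts.

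At stake are power in a small trial and the clarity of the efficacy statement that will be published and will inform the design of a later trial.

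**Working it through.** **Inputs.** From section 2.5: N = 60 (30 per arm), power 0.99, a medium effect, four assessments. Alpha of 0.05 is read from the 95% CI. Assumed, because the article does not give them: Cohen's f = 0.25 for a medium effect; correlation between assessments rho = 0.5 (range 0.3 to 0.7); equal variances and correlations over time.

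**Step 1: the plan's own figure.** lambda = f² × N × m/(1 - rho), with df = (m - 1) and (N - 2)(m - 1).

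- m = 3: lambda = 0.0625 × 60 × 3/0.5 = 22.5, df 2 and 116, power 0.991. The smallest N for 0.99 is 60.
- m = 4: lambda = 30, df 3 and 174, power 0.998. The smallest N for 0.99 is 50.

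So 60 matches a three-assessment calculation, and for four assessments it is more than f = 0.25 requires. A sustained arm difference d at T1 to T3 gives lambda = (60/4) × 0.75d²/0.5 = 22.5d². Setting this equal to 30 gives d = 1.15. The 0.99 therefore corresponds to a sustained difference of about 1.15 SD, and at that size every candidate test has power near 1. The comparison below uses d = 0.5, which is an assumption.

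**Step 2: power at N = 60, rho = 0.5, sustained d = 0.5.**

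- *Interaction with T0 as a response.* The arm differences are (0, 0.5, 0.5, 0.5), with sum of squares about their mean 0.1875. lambda = 15 × 0.1875/0.5 = 5.625, df 3 and 174, power **0.48**.
- *Same 3-df test adjusted for T0.* Residual variance 1 - rho² = 0.75 and covariance rho - rho² = 0.25. lambda = 15 × [3 × 0.25/(0.75 + 2 × 0.25)] = 9.0, power **0.70** on the same df.
- *Baseline-adjusted T1 contrast.* ncp = 0.5/sqrt((4/60) × 0.75) = 2.24, power **0.59**.
- *Baseline-adjusted mean of T1 to T3.* Residual variance (1 + 2 × 0.5)/3 - 0.25 = 0.417. ncp = 0.5/sqrt((4/60) × 0.417) = 3.0, power **0.84**.

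**Step 3: other time courses and correlations (same formulas).**

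| Differences at T1, T2, T3 | rho | Interaction | 3-df adjusted for T0 | T1 adjusted | Mean adjusted |
|---|---|---|---|---|---|
| 0.5, 0.5, 0.5 | 0.3 | 0.35 | 0.67 | 0.51 | 0.82 |
| 0.5, 0.5, 0.5 | 0.5 | 0.48 | 0.70 | 0.59 | 0.84 |
| 0.5, 0.5, 0.5 | 0.7 | 0.72 | 0.83 | 0.76 | 0.93 |
| 0.5, 0.35, 0.2 | 0.5 | 0.36 | 0.49 | 0.59 | 0.54 |
| 0.2, 0.35, 0.5 | 0.5 | 0.36 | 0.49 | 0.14 | 0.54 |
| 0.5, 0, 0 | 0.5 | 0.48 | 0.51 | 0.59 | 0.17 |

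Adjusting for T0 raises the power of the 3-df test in every row. The gain is large for a sustained effect and small for an effect at T1 only. Each single contrast loses to the interaction in at least one row.

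**Step 4: false positives.** One interaction test per outcome holds its level: 4.7-5.4% in 20,000 simulated null trials per setting. Over two primary outcomes the chance of at least one false positive is 9-10% (1 - 0.95² = 9.75% if independent). If each primary outcome were instead tested separately at T1, T2 and T3 at 5%, it would be 20-26%, depending on the assumed correlations (1 - 0.95⁶ = 26.5% if independent).

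**The case against.** **The plan is a pilot and the article is condensed.** The baseline parametrisation, the primary contrast and multiplicity handling are often left to an analysis plan, which is not shown. Section 2.5 also allows linear mixed models, and a model with T0 constrained equal across arms is itself fitted with time-by-group terms. This stands in part. If that model is intended, only a clarifying sentence is needed. But section 2.5 does state the test, the four assessments and the kinds of covariate, and its ordinary reading leaves T0 as an outcome.

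**The interaction test is robust to the time course.** This stands. For an effect at T1 only, the mean contrast has 0.17 against 0.48. For a growing effect, the T1 contrast has 0.14 against 0.36. It is an argument for choosing the contrast with care. It does not count against adjusting for T0.

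**On the stated inputs nothing is lost.** At f = 0.25 the interaction has 0.998. That is true, but it reflects an implied sustained difference of about 1.15 SD.

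A reader might also infer three stronger points that the article does not support:

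- *That the interaction test itself gives many chances of a false positive.* It does not. It protects against multiplicity over time, and section 2.5 does not plan six separate tests.
- *That the and/or wording is a formal success rule.* It is a description in the design and expected-results sections, and no decision rule is given.
- *That the result decides whether a larger trial follows.* Sections 3 and 5 foresee a larger trial without any such condition.

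**Conclusion.** The point holds as an improvement to the analysis. As ordinarily read, the planned test leaves T0 unadjusted, and the description of preliminary efficacy names no primary time. For a sustained 0.5 SD difference with 60 completers and correlation 0.5, adjusting for T0 raises the power of the 3-df test from 0.48 to 0.70. A well-chosen single contrast can reach 0.84. The gain from adjustment appeared in all patterns tried over correlations of 0.3 to 0.7. The gain from a single contrast depends on the true time course.

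The type I error issue is modest as the plan is written: about 5% per outcome and about 10% over the two primaries. The 20-26% figure is conditional on a procedure that the plan does not state.

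These sizes rest on the assumed d, correlation and compound symmetry, none of which the article gives, and on 60 participants actually being evaluable. The result will inform the later trial, not decide it.

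**What to change.** 1. In section 2.5, state that the mixed model uses the T0 value of the outcome as a covariate, or constrains the T0 mean to be equal across arms, with T1 to T3 as the responses of interest.
2. For each primary outcome, name in advance one baseline-adjusted between-arm contrast, such as T1 or the mean of T1 to T3. Choose it from the time course that the team expects, and give the reason.
3. Base the preliminary-efficacy statement on those contrasts in place of the and/or wording in sections 2.1 and 3.
4. Report other time points and the secondary outcomes as estimates with 95% confidence intervals.

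Ordering the two primary outcomes is optional. Table 1 marks them equally, and an order would be the team's preference. If both are tested at 5% without an order, say that the chance of at least one false positive is about 10%.

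The cost is wording only: no added participants, assessments or instruments. The one real downside is lower power if the true time course does not match the chosen contrast.
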